#### Assessing impact

CHPS+ will have core, intermediate outcome, and process endpoints, each requiring systems of data capture, data management, and analysis to gauge project impact. These core endpoints and indicators will be consistent with the Ghana Ministry of Health core indicators of health improvement with instruments designed to maximize comparability with national Ghana Demographic and Health Survey instruments. This will involve indicators of under-five mortality, infant mortality, and neonatal mortality by gender of child; age specific and total fertility rates and proximate determinants that are relevant to policy; and indicators of parental health seeking behavior, such as skilled attendant delivery, care of sick children, exposure to community-based services, distance to health facility and utilization of facilities for essential care. Critical covariates essential to the understanding of equity and impact, such as educational attainment, household economic status, and distance to service point will also be assessed.

CHPS+ will utilize impact assessment strategies that have worked well for GEHIP. Routine compilation of time trends indicators will be supplemented with end-of-project *difference-in-differences* calculations for each indicator. This econometric strategy has been applied elsewhere for the assessment of non-randomized plausibility trials [44–46] and successfully applied to the evaluation of GEHIP [47]. The procedures involve collecting data in baseline clusters, monitoring systems changes and the timing of these changes, and repeating the survey in baseline clusters with a separate endline stage two sample to gauge effects. Regression analysis is based on merged baseline and endline data for the estimation of parameters that control for baseline differences and contextual confounders, changes over time that are unrelated to interventions, and conditional effects of interventions that control for these confounding changes by estimating net intervention effects. A difference-in-difference estimate of program effects is given by the child survival effect of CHPS+ systems interventions (**S**) where individual child i is scored 1 if the household is located in a cluster that is exposed to CHPS treatment and zero otherwise and z is scored 1 if the case *i* is observed in the endline and zero if the case is observed in the baseline. If all covariates are equal to zero for child *i*, (*i.e.,*
*X*_*1*_*=**0*, *X*_*2*_*=**0,...*
*X*_*k*_*=**0,*
*S=0,*
*Z=0*), the underlying mortality hazard is *h*_0_(t) and the conditional multilevel proportional hazard model is:1$$ {\boldsymbol{h}}_{x\sim SZ}\left(\boldsymbol{t}\right)={\boldsymbol{h}}_{\mathbf{0}}\left(\boldsymbol{t}\right){\boldsymbol{e}}^{\left[{\beta}_0+\sum \limits_{k=1}^K{\beta}_k{X}_{ij k}+\gamma {S}_j+\delta {Z}_{ij}+\zeta {S}_j{Z}_{ij}+{\mu}_j+{\varepsilon}_{ij}\right]} $$for all *t*, where:

*X̃*_*i*__*j*__*k*_ represents *K* characteristics of child *i* in cluster *j*;

*S*_*j*_ indicates whether cluster *j* is in the treatment area (*S* = 1) or comparison area (*S* = 0);

*Z*_*ij*_ indicates whether the person time of child *i* in cluster *j* occurs during the post-treatment period (*Z* = 1) or pre-treatment period (*Z* = 0);

*S*_*j*_*Z*_*ij*_ is a cross-level interaction term of treatment and period for estimating the net effect of treatment in the difference-in-differences approach;

and

*μ*, *ε* represent residuals for cluster and individual levels, respectively.

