### The CHPS+ program

In keeping with Ghana’s legacy of evidence-based health system programming, the GEHIP success is being transitioned into a replication trial phase that will develop, test, and disseminate a strategy for reforming CHPS based on GEHIP lessons learned. Its continuous functioning will provide a learning platform for informing national efforts to scale-up GEHIP strategies through an initiative known as the *Program for Strengthening the Implementation of the Community-based Health Planning and Services Initiative in Ghana (CHPS+).* Launched in 2016 as a five-year project, CHPS+ aims to strengthen the capacity of District Health Management Teams (DHMT) to oversee improvements in the quality of primary health care, focusing in particular on family planning and maternal, newborn and child health care delivery. CHPS+ is comprised of a program of applied learning, team problem solving, peer mentoring, incentivizing financing for improving basic equipment requirements, and technical training that strengthens Ghana’s health system at all levels. It is designed with the intention of decentralizing reform of CHPS implementation activities, with GEHIP lessons learned providing a guide to strategic planning and action. As such, CHPS+ represents a program of research on the utilization of GEHIP research -- the science of which differs from the science of implementing and evaluating a ‘proof of concept’ trial.

This application of implementation research is not new. Organizational change research is a scientific endeavor of management science that is grounded in decades of theory, methods, and application [14–16]. However, scientific investigation of scaling up is only rarely applied to health systems research projects in Africa [17].

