## Methods/design

### Hypotheses and goals

CHPS+ will test the primary implementation hypothesis that the pace of expansion of CHPS population coverage can be significantly increased relative to the pace of CHPS expansion in districts not yet exposed to CHPS+ interventions. Research is also designed to test the impact hypothesis that CHPS+ implementation will improve infant and child survival. A three component mixed method evaluation strategy has been launched for program evaluation involving: i) baseline and endline randomized cluster sample survey research with 247 census enumeration clusters dispersed in 14 districts of the Northern and Volta Regions for assessing the effect of cluster exposure to CHPS+ activities on childhood survival; ii) a service delivery point monitoring system for assessing the association of changes in service system readiness with CHPS+ interventions; and iii) a program of qualitative systems appraisal (QSA) to gauge stakeholder perceptions of systems problems, reactions to CHPS+ interventions, and perceptions of change. Temporal variance in project implementation will be monitored to provide stepped wedge recorded differential exposure to operations. Integrated survey and M&E data will permit multi-level longitudinal models of impact; longitudinal QSA data will provide data on the implementation process.

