#### Sample design

The sampling frame for the first stage was from the 2010 Population and Housing Census which provided a complete listing of Enumeration areas in the fourteen districts to be surveyed. The sampling frame contained information such as the location and estimated number of households. In each region, Enumeration areas were stratified by rural versus urban and by the estimated number of households in the cluster. Clusters were stratified into three groups (small, medium, or large yielding a total of 6 strata in each district. Enumeration areas were sampled from each stratum using probability proportional to population size (PPS). Weights will be applied at the cluster level to standardize probabilities of household selection based on the relative population size of clusters.

To obtain a sampling frame for the second-stage sampling, a household listing of all households in each cluster was compiled based on census information on household size and number women of reproductive age (15–49) in each household. Households were then stratified into three strata defined by the number of eligible women in each household.

To maximize sample efficiency for difference-in-difference estimation at the endline, baseline sample clusters will be reused without modification to permit longitudinal observation of clusters and the assessment of the average treatment effect arising from the timing of exposure of clusters to project interventions. The second-stage sampling procedure will be repeated, yielding a household sample for the longitudinal observation of children exposed versus unexposed to interventions over the duration of the project, with provision for statistical adjustment of baseline and endline differentials and changes in project endpoints that are unrelated to CHPS+ interventions.

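### The period indicator Z has two definitions, survey round and pre/post person-time; they agree only if endline person-time is limited to time after exposure, and otherwise survey-round coding pulls the effect toward no effect

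*Protocol article*

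**What the plan says.** Under Assessing impact, the protocol article defines the period indicator twice for the same model.

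- In the text leading into Equation 1, it is 1 if the case "is observed in the endline and zero if the case is observed in the baseline". This is survey of origin and is fixed for each child.
- In the list of terms under Equation 1, it depends on whether the child's person-time "occurs during the post-treatment period" or in the pre-treatment period. This is calendar time relative to treatment and can change within one child's life.

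The product of S and Z "is a cross-level interaction term of treatment and period for estimating the net effect of treatment in the difference-in-differences approach". In the equation S carries only a cluster index: it marks treatment or comparison area and holds no start date.

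Three other statements bear on how Z should be coded.

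- Length: CHPS+ was "Launched in 2016 as a five-year project" (The CHPS+ program).
- Timing: "Temporal variance in project implementation will be monitored to provide stepped wedge recorded differential exposure to operations" (Hypotheses and goals). Sample design adds that the reused clusters are meant to permit "the assessment of the average treatment effect arising from the timing of exposure of clusters to project interventions".
- Data source: the endline means "repeating the survey in baseline clusters with a separate endline stage two sample to gauge effects", with questionnaires modelled on the 2014 national Demographic and Health Survey.

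**The concern.** The coefficient of S×Z, zeta, is the child-survival effect. Two codings of Z are therefore two estimands unless they select the same person-time.

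The endline draws a new household sample, so baseline children are not followed forward. Survival time and deaths among endline children must be reported retrospectively. In a cluster that was exposed late, a child in the endline sample may have lived, or died, before exposure began. The survey-round definition codes that time as post-treatment; the person-time definition codes it as pre-treatment.

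Under the survey-round definition, unexposed experience in treatment clusters enters the cell with S = 1 and Z = 1. If the intervention helps, this moves zeta toward zero. At stake is the test of the impact hypothesis on infant and child survival, for which the household survey was sized.

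**Working it through.** **Plan's own figure.** The article states 80% power at the 5% level for a 15% reduction in under-five mortality in each region. This cannot be recomputed from the article, which gives no values for the intra-cluster correlation, baseline mortality, households per cluster or children per woman. The figure is not disputed here and serves as the starting point.

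**Inputs from the article.** 15% reduction, taken as a hazard ratio (HR) of 0.85; 80% power; 5% level (sidedness not stated, two-sided assumed).

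**Assumed input.** f, the share of expected endline deaths that falls before exposure. The article gives no recall window, survey dates or cluster start dates, so f can only be varied. Baseline person-time is taken as unexposed under either coding.

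**Dilution.** Under survey-round coding the estimated hazard ratio is about

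HR(f) = f + (1 − f) × 0.85

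- f = 0: 0.85
- f = 10%: 0.10 + 0.90 × 0.85 = 0.865
- f = 20%: 0.20 + 0.80 × 0.85 = 0.88
- f = 40%: 0.40 + 0.60 × 0.85 = 0.91

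**Power.** Hold the information at the amount that gives 80% at HR 0.85. The standardised effect there is 1.960 + 0.842 = 2.802, so

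power(f) = Φ(2.802 × ln HR(f) / ln 0.85 − 1.960), with ln 0.85 = −0.1625

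- f = 10%: 71%
- f = 20%: ln 0.88 = −0.1278, ratio 0.787, Φ(2.204 − 1.960) = Φ(0.244), about 60%
- f = 40%: ln 0.91 = −0.0943, ratio 0.580, Φ(1.626 − 1.960) = Φ(−0.334), about 37%

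**Check on the difference-in-differences scale.** Let treatment areas start 10% higher and let a 10% secular fall apply to both arms. The baseline ratio is 1.1.

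- f = 20%: comparison endline rate 0.20 + 0.80 × 0.90 = 0.92; treatment endline rate 1.1 × (0.20 + 0.80 × 0.90 × 0.85) = 0.8932; ratio of ratios (0.8932 / 0.92) / 1.1 = 0.883
- f = 40%: comparison 0.40 + 0.60 × 0.90 = 0.94; treatment 1.1 × (0.40 + 0.60 × 0.90 × 0.85) = 0.9449; ratio of ratios 0.914

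Both are close to the simple formula, and the direction is the same.

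**Why f must count deaths, not person-time.** Under-five risk is concentrated early in life. As an illustration, assume births uniform over the five years before the endline, with 45% of under-five hazard in the first month, 25% in the rest of the first year and 30% at ages one to four. None of these values is in the article.

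| Exposure began, years before endline | Person-time before exposure | Expected deaths before exposure | Estimated HR | Power |
|---|---|---|---|---|
| 5 | 0% | 0% | 0.850 | 80% |
| 4 | 4% | 14% | 0.871 | 67% |
| 3 | 16% | 32% | 0.899 | 45% |
| 2 | 36% | 53% | 0.930 | 24% |

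A person-time share put into the formula would understate the dilution.

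**The case against.** The strongest reply is that the list under Equation 1 is the formal definition, already uses person-time, and describes S×Z as an interaction of treatment and period. The sentence before the equation would then be a loose lead-in, and dilution would arise only if an analyst followed it. The two wordings might also coincide: Sample design speaks of observing children over the duration of the project, and a five-year window matched to five years of exposure gives f = 0. Recall windows, dates and episode-splitting are also details that an article commonly leaves to the full protocol or analysis plan.

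Part of this stands. The missing dates and window are not a fault of the article, and they prevent any firm figure. The rest does not remove the point. Both definitions are stated rules for the same symbol, nothing says which prevails, and no passage cuts endline time at the start of exposure. The staggered timing that the article intends to use also makes f = 0 in every treatment cluster unlikely.

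Some stronger readings are tempting but unsupported:

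- **A dilution of known size.** The article fixes no value of f.
- **A required multiple of the sample.** Squared ratios of log hazard ratios, such as (0.1625 / 0.1278)² = 1.62 at f = 20%, are information ratios. In a clustered design that reuses its clusters, they do not convert simply into sample size.
- **A child whose life straddles the start date cannot be coded.** The missing time index on Z leaves this unclear, but the definition attaches Z to person-time, so the unit of analysis could be an episode.
- **A choice of coding will be made after seeing the data.** The conflict leaves room for it, but an analysis plan not shown here may already settle it.

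**Conclusion.** The point holds as a contradiction between two stated definitions of the variable that forms the effect estimate, with a conditional bias of known direction. Survey-round coding biases zeta toward no effect whenever treatment-cluster children in the endline contribute time from before exposure and the intervention is beneficial. The illustrated losses, to about 60% power at f = 20% and 37% at f = 40%, assume a true hazard ratio of 0.85, fixed information and a two-sided 5% test. They show sensitivity and do not predict this trial's result; with all endline time after exposure, the loss is zero. The conflict should be resolved before the endline analysis, because one of the two rules, followed as written, can give a wrong answer.

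**What to change.** 1. Delete the survey-round definition of Z in the text before Equation 1. Keep the person-time definition and give it a time index.
2. Split each child's record at the start of exposure and keep earlier time reported at the endline as unexposed.
3. Replace the single S×Z term with a cluster-specific, time-varying exposure indicator, plus calendar-period terms applied to both arms. One common start date would not be enough: with staggered exposure, treatment clusters that enter later would still have unexposed time coded as treated.
4. Carry survey round as a separate covariate, so that differences in reporting between the surveys are not absorbed into the period effect.

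The article already plans to monitor the timing of implementation, so no new data collection is implied. The cost is a wording change, episode-splitting in the analysis code and a few extra nuisance parameters.

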**Fig. 1 Fig1:**
[figure not shown]
The Percentage of District Populations Covered by Functional CHPS Services in GEHIP Intervention Versus Comparison Districts

Interventions that enabled these achievements to be attained in five years included strengthening CHPS by expanding the role of community health nurses (including midwives) and volunteers in maternal, newborn and child health, and improving their skills in life saving interventions such as conducting neonatal resuscitation, kangaroo mother care, and care for febrile illnesses. Other interventions included the provision of family planning (FP) and reproductive health (RH) services, training of nurses in Integrated Community Case Management (ICCM), improving the leadership capabilities of nurses and their supervisors through training, and improving logistics supplies and management.

Each participating district was provided with a modest commitment of supplemental funding over a three-year period, providing a basis for exchanges, budgeting, and community engagement to be appropriately focused on CHPS start-up activities. Classroom sessions were minimized; instead, systems strengthening activities were launched in conjunction with community engaged frontline worker training in interventions and peer exchanges to demonstrate teamwork and practical task planning. Emergency referral capacity was instituted with an approach that links worker training to community mobilization and information support; perinatal interventions; and volunteer recruitment, training, and support. The outcome was an approach to integrated services that expanded the coverage and quality of Integrated Management of Childhood Illnesses (IMCI) services and responsiveness to emergency care needs. By linking grassroots politicians to community efforts, the popularity of health development was demonstrated in ways that built political commitment to leveraged financing of health sector investment in CHPS. Community volunteerism, catalytic resources, politically inspired development investment, and sustained diplomatic support from district health officials worked as a system of interaction that transformed CHPS implementation.

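### Equation 1 holds the area, period and treatment hazard ratios constant over all under-five ages; zeta is biased if the areas differ in age pattern and either the secular decline or the age mix of follow-up also differs

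*Protocol article*

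**What the plan says.** Assessing impact gives a difference-in-differences hazard model, introduced as "the conditional multilevel proportional hazard model is" Equation 1. It is written to apply at every age t. The area term "indicates whether cluster *j* is in the treatment area"; the period term is 1 when a child's person-time "occurs during the post-treatment period"; and their product "is a cross-level interaction term of treatment and period for estimating the net effect of treatment in the difference-in-differences approach". Each has one coefficient. The baseline hazard may take any shape over age, but the three ratios may not vary with age. No age-by-area or age-by-period term is printed.

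The same section supports the method by its earlier use in non-randomised plausibility trials. It lists "indicators of under-five mortality, infant mortality, and neonatal mortality by gender of child" among the endpoints and plans a difference-in-differences calculation for each indicator. Hypotheses and goals states the impact hypothesis as "CHPS+ implementation will improve infant and child survival". The Background, after Fig. 1, describes the parent programme as including "conducting neonatal resuscitation, kangaroo mother care, and care for febrile illnesses".

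**The concern.** One gamma assumes that treatment and comparison areas have the same age pattern of mortality. One delta assumes that the secular change is the same proportion in neonates and in older children. Without randomisation, nothing in the design secures the first, and the second is an assumption about background trends.

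If both fail, the areas show different overall declines even though their trends are identical at each age, and the difference goes into zeta. The same happens if the areas differ by age and the post-treatment period holds relatively less follow-up at older ages than the pre-treatment period. This error does not shrink with more clusters, and it falls on under-five mortality, the outcome on which the survey is sized.

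A single zeta is also an average over ages, in a programme whose predecessor had both newborn and later-childhood components.

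**Working it through.** **From the article.** The model form is Equation 1. The target is a 15% reduction in under-five mortality with 80% power at the 5% level in each region (Impact research: The household survey), read here as a hazard ratio of 0.85, so ln 0.85 = -0.163. The power figure cannot be reproduced, because baseline mortality, intra-cluster correlation, children per woman and households per cluster are not printed. The point does not depend on it.

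**Assumed.** Three age bands (0-27 days, 1-11 months, 12-59 months), no programme effect, and the same decline in both areas at each age. Covariates and random effects are left out.

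**Formula.** With a common age baseline and free terms for the four area-by-period cells, the fitted model reproduces total deaths in each cell. If the two areas have the same age distribution of person-time within each period, then

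exp(zeta) = (T_post / C_post) / (T_pre / C_pre),

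where T and C are total deaths in treatment and comparison areas. With no programme effect the answer should be 1.

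**Cases with no bias.**
- Neonatal shares of deaths 50% and 40%, uniform 20% decline, same age mix: 0.80 / 0.80 = 1.000.
- Area ratios of 1.0, 1.1 and 1.5 in the three bands, uniform decline, same age mix: 1.000.
- Constant area ratio, decline varying by age: 1.000.

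**Mechanism (a): area pattern and decline both vary by age.** Declines of 10%, 25% and 35% leave 0.90, 0.75 and 0.65. Non-neonatal deaths are split equally between the two later bands. The overall fraction remaining is:
- shares 55/22.5/22.5: 0.4950 + 0.16875 + 0.14625 = 0.810
- shares 50/25/25: 0.4500 + 0.1875 + 0.1625 = 0.800
- shares 45/27.5/27.5: 0.4050 + 0.20625 + 0.17875 = 0.790
- shares 40/30/30: 0.3600 + 0.2250 + 0.1950 = 0.780

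| Neonatal share, treatment v comparison | exp(zeta) | Size relative to 0.163 |
|---|---|---|
| 50% v 40% | 0.800/0.780 = 1.026 | 0.025/0.163 = 16% |
| 40% v 50% | 0.780/0.800 = 0.975 | 16% |
| 55% v 40% | 0.810/0.780 = 1.038 | 0.038/0.163 = 23% |
| 50% v 45% | 0.800/0.790 = 1.013 | 0.013/0.163 = 8% |

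Splitting the non-neonatal deaths anywhere from 40:60 to 70:30 moves each ratio by less than 0.005.

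**Mechanism (b): area pattern varies by age and the age mix shifts.** Comparison deaths before treatment are 40, 30 and 30. Area ratios of 1.0, 1.1 and 1.5 give treatment deaths of 40, 33 and 45, so T_pre / C_pre = 118/100 = 1.180. The decline is a uniform 15%.
- Older-age person-time in the post period cut to 50%: C_post = 34 + 25.5 + 12.75 = 72.25; T_post = 34 + 28.05 + 19.125 = 81.175; ratio 1.1235; exp(zeta) = 1.1235/1.180 = 0.952.
- Cut to 30%: C_post = 34 + 25.5 + 7.65 = 67.15; T_post = 34 + 28.05 + 11.475 = 73.525; ratio 1.0949; exp(zeta) = 0.928.
- Opposite direction, area ratios 1.4, 1.2 and 1.0, cut to 50%: T_pre / C_pre = 122/100; post ratio 107/85 = 1.2588; exp(zeta) = 1.2588/1.220 = 1.032.

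Varying the neonatal share from 40% to 50% and the later split from 40:60 to 60:40 gives 0.946 to 0.964 for the first of these and 0.917 to 0.947 for the second.

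**Against sampling error.** If the stated 80% power applies to zeta, two-sided (sidedness is not stated), the regional standard error is 0.163 / (1.960 + 0.842) = 0.058. The biases are then about 0.2 to 0.6 standard errors under (a), and 0.8 to 1.3 for the first two cases under (b).

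**With gamma and delta by band.** Refitting the expected counts as a Poisson piecewise-exponential model returned exp(zeta) = 1.000 for the (a) cases and for the 50% and 30% cuts with area ratios 1.0, 1.1 and 1.5. The standard error of zeta rose by about 0 to 3%.

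**What one zeta can show.** With no area or period differences and death shares 40/30/30, true treatment ratios of 0.70, 0.85 and 1.00 give 0.280 + 0.255 + 0.300 = 0.835. The opposite profile, 1.00, 0.85 and 0.70, gives 0.400 + 0.255 + 0.210 = 0.865. The two are hard to tell apart.

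**The case against.** The strongest reply has five parts.

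- **Age differences between areas are harmless alone.** A reader might infer that ordinary age differences between non-randomised areas are enough to create a false programme effect. They are not: those cases give exactly 1.000. A second condition is always needed, and the article establishes neither an age-varying decline nor a shifted age mix. This stands and limits the point.
- **Age effects are not hidden.** A reader might infer that the plan cannot see age-specific effects. The article plans difference-in-differences for neonatal and infant mortality as well as under-five. An absent neonatal effect beside a clear under-five effect would be visible. This stands. It does not repair the under-five estimate itself, and no listed indicator isolates 12-59 months.
- **Proportionality checks and age interactions usually sit in an analysis plan that is not shown.** Their absence is indeed no finding. The point is about a model that is printed with constant ratios.
- **The shifted age mix depends on what the period term means.** The text before Equation 1 scores it by survey round, whereas the definitions below it use the timing of person-time. If it is survey round with equal recall windows, mechanism (b) need not arise. This stands.
- **The sizes rest on assumptions.** Areas are compared within region, so large differences in age pattern may be unlikely, and the newborn and febrile-illness components are described for the predecessor programme. This stands and is why the sizes are shown only as a range.

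**Conclusion.** Equation 1 as printed constrains gamma, delta and zeta to be constant over the whole under-five age range. The under-five zeta is exposed to bias in either direction when the areas differ in age pattern and, in addition, either the secular decline differs by age or the age mix of person-time shifts between periods. Under the assumed inputs the false hazard ratio is about 0.97 to 1.04 for the first route and about 0.93 to 0.95 for a strongly shortened older-age post window, against a target of 0.85. Milder assumptions give less, and with either condition missing the bias is nil.

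The documents do not show that the bias will occur, only that the printed model does not guard against it. The case for acting is that protection costs almost nothing, not that the estimate is known to be wrong.

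**What to change.** Split each child's follow-up at 28 days and 12 months. Let gamma and delta take separate values at 0-27 days, 1-11 months and 12-59 months. Keep one common zeta as the headline and describe it as an average over ages. Report band-specific zetas as secondary results beside the planned neonatal and infant analyses. State whether the period term follows survey round or person-time, and give the pre- and post-treatment windows.

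Replacing the headline with a five-year risk ratio built from band-specific zetas is a debatable trade-off, better kept as secondary reporting.

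Cost: a change of wording and a few lines of code. No new data are needed, since any hazard model of child survival already requires age at death. There are four extra nuisance parameters (two further bands for each of gamma and delta), a standard error for zeta at most about 3% larger in the cases computed, and wide intervals for the band-specific estimates.
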